## Introduction

Hyperthyroidism is a common condition affecting 3% of women and 0.3% of men in the UK.^1^ Common clinical features indicating hyperthyroidism include weight loss, heat intolerance, tremor, palpitations and anxiety.^2^ Treatment is critical to minimise complications including atrial fibrillation and stroke that contribute to the observed 20% increase in mortality.^3^

There are three treatment options: antithyroid drugs (ATDs), radioactive iodine (I-131, radioiodine) or surgical, either as a total or hemithyroidectomy. ATDs are associated with a high rate of relapse (30%–70%),^4^ while treatment with radioiodine or thyroidectomy leads to the development of hypothyroidism, requiring lifelong levothyroxine replacement, which is seen in 80% of patients administered radioiodine and up to 100% undergoing thyroidectomy. Guidance recommends discussion of all three options with the patient.^5 6^ There is insufficient evidence to recommend one treatment over the others, although some studies indicate differences in cardiac events and mortality between the treatment modalities.^7 8^

Weight gain following various treatments for hyperthyroidism has been described.^9 10^ Clinicians commonly assume that the observed weight gain is a simple regain of weight lost prior to the initiation of treatment. However, an analysis of 1373 patients with hyperthyroidism has demonstrated a higher prevalence of obesity at 3 years of follow-up when compared with the age-matched and sex-matched background population (37% vs 26% in men, p<0.001; 32% vs 26% in women, p<0.001).^11^ These findings suggest excess weight gain beyond patients’ premorbid weight (weight overshoot). Additionally, the study showed significant differences in final weight gain compared with baseline between those treated with ATDs (5.4 kg, 95% CI 4.8 to 6.0) and those who received radioiodine but did not develop hypothyroidism (5.1 kg, 95% CI 4.3 to 6.1) when compared with those treated with radioiodine who developed subsequent hypothyroidism (7.1 kg, 95% CI 6.6 to 7.7). The extent of weight change in patients treated with thyroidectomy was not evaluated.

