### Population

Adult patients (≥18 years) who were for the first time diagnosed with hyperthyroidism (the list of codes in online supplemental appendix) between 1 January 1996 and 31 December 2015 will be eligible for inclusion. To minimise missed cases, the diagnosis will be additionally identified by a prescription of carbimazole or propylthiouracil, which are ATDs indicated only for treatment of hyperthyroidism. A minimum of 12 months of data must be available before the date of diagnosis and after the index date. CPRD records need to be classified as acceptable research quality.

10.1136/bmjopen-2021-055219.supp1Supplementary data

Exclusion criteria encompass ATD treatment of duration shorter than 6 months as the only treatment, that is, with no radioactive iodine or thyroidectomy followed. This is to avoid contamination by misdiagnosis or spontaneously resolving thyroiditis. Patients treated with both definitive treatment methods, that is, radioiodine and thyroidectomy, will also be excluded. However, ATD treatment followed by either radioiodine or thyroidectomy (one of the definitive treatments) is considered a pretreatment and does not constitute an exclusion criterion.

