### Confounding

Based on the literature and clinical experience, we identified a number of confounders affecting both the exposure and the outcomes of our study. The modelled outcomes will be adjusted for baseline data (sex, age, IMD quartiles, smoking status and comorbidities) and time-varying covariates (thyroid function, cumulative time on the medical treatment, time since diagnosis, levothyroxine replacement, pregnancy and diagnosis of cancer). Table 2 presents the details of how covariates are defined and handled. Figure 1 depicts the directed acyclic graphs representing the relationship between the covariates. We will explore the relationships between the potential confounders and both exposures and outcomes independently in order to establish their potential role in this particular dataset.

**Table 2 T2:** Definitions of study covariates

Variable	Definition
Aetiology of hyperthyroidism	Identified based on Read codes and categorised in (1) Graves’ disease, (2) toxic nodular goitre and (3) undefined. The undefined category will consist of unspecified diagnosis and missing aetiology data.
Age	Age at index date
Baseline fT4	The highest measurement between 3 months prior to diagnosis and the index date
BMI	Normal (or underweight) <25 kg/m^2^, overweight 25–30 kg/m^2^ and obese ≥30 kg/m^2^; additionally, BMI status will be deduced from the Read code
Cancer diagnosis	Switch-type binary variable assuming lifelong status of cancer comorbidity
Frequency of GP visits	Time-varying variable of number of GP visits in a unit of time
IMD	IMD will be stratified into quintiles.
Levothyroxine (LT4) replacement	Switch-type binary variable assuming lifelong LT4 administration following development of hypothyroidism in radioiodine and thyroidectomy treatment groups
Pregnancy	Time-varying binary variable recording pregnancy
Pretreatment ATD	Cumulative time on ATD between diagnosis and the index date
Sex	Binary variable
Smoking status	As recorded at the index date, last observation carried forward if not available at the index date
TSH	Serial TSH, log-transformed for the analysis
Time since diagnosis	Time-varying variable measuring cumulative time since diagnosis

ATD, antithyroid drug; BMI, body mass index; GP, general practitioner; IMD, Index of Multiple Deprivation; TSH, thyroid-stimulating hormone.

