### Index date and follow-up

The index date in the cohort is the date of initiation of treatment for hyperthyroidism, which defines the treatment group (either ATD, radioiodine or thyroidectomy). There is a requirement of at least 12 months’ data available prior to the index date.

The natural history of weight changes will be modelled preindex and postindex date. While the follow-up for the analysis of outcomes will start at the index date, a minimum of 12-month follow-up is required for the inclusion.

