#### Cardiometabolic risks and mortality

The descriptive analysis of primary and secondary outcomes will provide useful summaries about the sample and the outcome measures. Besides the unadjusted descriptive statistics, such as the incidence rate of each outcome, simple graphics analysis will be provided.

Causal inference in the analysis of cardiometabolic outcomes and mortality will be undertaken using inverse propensity weighting (IPW). This method was empirically shown to be superior to other propensity score-based approaches in analysis of multiple treatments with a binary outcome.^27^ The propensity-score matching, even though well valuated in two-arm treatment, in multiple treatments might introduce bias; the IPW is more efficient in such scenario. Additionally, IPW method is more flexible and requires weaker unconfoundedness assumption.^28^

Generalised propensity weights with treatment category as dependent variable will be calculated in the multinominal logistic model.^29^ The model will be developed using the following covariates: age at the index date, sex, baseline serum fT4, aetiology of hyperthyroidism, smoking status, IMD, cumulative time on ATD between diagnosis and the index date, time since diagnosis and BMI status.

Variables related to treatment, as an outcome, at p<0.10 will be selected for inclusion in the multiple propensity weights.^30^ To identify these variables, we will conduct several regression analyses with the treatment as a dependent and each potential confounder as an independent variable. Furthermore, it will be investigated whether adding interaction terms or higher-order terms for continuous variables will improve the balance of the model. The Hausman test will be used to check the independence of irrelevant alternatives assumption, which is the main assumption of multinomial regression analysis.^30^ If this assumption is not met, multinomial probit analysis will be used instead.

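### Baseline fT4 is the maximum over a window whose length depends on treatment group, so weighting on it distorts severity at diagnosis in the secondary comparisons

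*Protocol article*

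**What the plan says.** Four statements in the protocol article bear on this point.

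- **Confounding, Table 2** defines baseline fT4 as "The highest measurement between 3 months prior to diagnosis and the index date".
- **Index date and follow-up** fixes the end of that window: "The index date in the cohort is the date of initiation of treatment for hyperthyroidism, which defines the treatment group (either ATD, radioiodine or thyroidectomy").
- **Population** states that "ATD treatment followed by either radioiodine or thyroidectomy (one of the definitive treatments) is considered a pretreatment", so in those patients the ATD course lies before the index date. Table 2 has a covariate for this interval, "Cumulative time on ATD between diagnosis and the index date", so the authors expect it to be non-zero for some patients.
- **Cardiometabolic risks and mortality** puts the variable in the multinomial propensity model, whose list begins "age at the index date, sex, baseline serum fT4, aetiology of hyperthyroidism, smoking status, IMD". It is the only thyroid-function measure in that list; log TSH appears only as a post-index, time-varying adjustment.

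The same section adds a screening rule, "Variables related to treatment, as an outcome, at p<0.10 will be selected for inclusion in the multiple propensity weights", and a balance check that looks for differences at p<0.05 on the included variables as recorded. Nothing in the article limits the fT4 window to the time of diagnosis or makes it equal across groups.

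**The concern.** A maximum can only stay the same or rise as its window lengthens, and here the length depends on the treatment received. In an ATD patient the window normally holds untreated values around diagnosis. In a definitive patient pretreated with ATD it also holds on-treatment values and any relapse peak before the procedure. The same relapse in an ATD patient falls after the index date and cannot enter the variable.

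One label thus covers severity at diagnosis in one group and the worst value up to the procedure in part of the others. Weights that equalise it put pretreated definitive patients with moderate disease at diagnosis but a later peak on a par with ATD patients who had severe disease at diagnosis. The comparisons at stake are the weighted ones: MACE, type 2 diabetes, heart failure, ischaemic heart disease, stroke and mortality.

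**Working it through.** The protocol gives no figure on this point to reproduce, so the check has two parts: the definitions side by side, then an illustrative simulation.

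**1. Definitions side by side**

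| | ATD group | Definitive, no ATD first | Definitive, ATD first |
|---|---|---|---|
| Window opens | 3 months before diagnosis | same | same |
| Window closes | ATD start | procedure | procedure |
| Pre-index ATD time | about 0 by construction | 0 | whole pretreatment course |
| Relapse on or after ATD can enter | no | no | yes |

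More measurements alone raise a maximum. For 1, 2, 3, 5 and 8 independent standard normal values, the expected maximum is 0, 0.56, 0.85, 1.16 and 1.42 SD.

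**2. Simulation (n = 200,000; two groups, 40% definitive)**

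Assumed, not in the document: diagnosis fT4 with mean 40 and SD 15; within-patient SD 5; relapse peak with mean *m* = 30 or 40 and correlation 0.5 with severity; all definitive patients pretreated. The pre-index relapse share is set to 0, 30%, 50% or 70%. This borrows the 30%–70% range that the Introduction gives for relapse on ATD, which is not the same quantity.

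- Severity: S = 40 + 15·gap·D + 15·ε₁, where D = 1 for definitive treatment.
- Diagnosis-window value: X₀ = S + 5·ε₂.
- Relapse peak: P = m + 0.5·(S − 40) + 15·√(1 − 0.5²)·ε₃.
- Recorded baseline: X = max(X₀, P) if D = 1 and relapsed; otherwise X₀.
- Weights: logistic model for D on X and X²; 1/p if D = 1, 1/(1 − p) if D = 0.
- Reported difference: (weighted mean, definitive − weighted mean, ATD) / 15.

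True severity equal (gap = 0):

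| Relapse share | Peak mean | Recorded fT4, unweighted | Recorded fT4, weighted | True diagnosis severity, weighted |
|---|---|---|---|---|
| 0 | 30 or 40 | about 0.00 | 0.00 | 0.00 |
| 30% | 30 | +0.05 | 0.00 | −0.05 |
| 30% | 40 | +0.12 | 0.00 | −0.11 |
| 50% | 30 | +0.08 | 0.00 | −0.08 |
| 50% | 40 | +0.21 | 0.00 | −0.18 |
| 70% | 30 | +0.11 | 0.00 | −0.10 |
| 70% | 40 | +0.29 | 0.00 | −0.26 |

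The recorded variable balances in every row while severity at diagnosis does not. If only 80% of definitive patients are pretreated (assumed), the smallest non-zero effect shrinks roughly in proportion: 0.048 × 0.8 ≈ 0.04 SD. The range is therefore about 0.04 to 0.26 SD.

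Definitive group truly 0.3 SD more severe: the difference is +0.30 before weighting and −0.01 to −0.18 after weighting on the protocol's variable. With a window common to all groups it is +0.03 after weighting; that residue is measurement noise. With equal severity, the common window gives 0.00.

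**3. What this could mean for an outcome**

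The document gives no fT4–outcome slope. If the hazard ratio per SD of diagnosis fT4 were 1.1 to 1.5 (assumed), the shift would be HR^δ: from 1.1^0.04 = 1.004 to 1.5^0.26 = 1.11, or about 0.4% to 11%.

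**The case against.** **fT4 up to time zero may be a proper confounder.** Follow-up starts at the index date, and confounders are normally measured up to that date. A relapse peak may prompt definitive treatment and also raise later risk; dropping it would leave that peak unbalanced. This stands, and it shapes the fix: pre-procedure fT4 should be kept, but as its own variable. It does not justify merging relapse fT4 with diagnosis fT4 under one label in some patients only.

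**The protocol's model has more in it than fT4.** Pre-index ATD time and time since diagnosis are also listed, and poor overlap triggers trimming. If trimming removed every pretreated definitive patient, the distortion would vanish, but under an assumed 80% pretreated only 20% of the definitive patients would remain. These covariates are near zero by construction in the ATD group, so they cannot be relied on to repair the fT4 definition. The positivity problem they raise is a separate matter and does not make this definition sound.

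**Other safeguards.** The p<0.10 screen gives no protection, because the artefact itself produces an association with treatment. Post-index log TSH in the outcome models captures later thyroid function, including relapse in the ATD group, but does not correct a baseline weight.

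**Stronger readings.** A reader might infer that weighting always introduces an imbalance where there was none. That holds only if true severity is similar; with a true gap of 0.3 SD, weighting left a smaller difference than no weighting, though of reversed sign. A reader might also take the 30%–70% relapse range as the share of definitive patients with a recorded pre-index peak and so treat the size as known. The Introduction's figure describes relapse on ATD, and the protocol does not give the other share.

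**Conclusion.** The point holds as a matter of definition. The baseline fT4 window is short in the ATD group and spans the pre-procedure ATD course in pretreated definitive patients. The variable enters the propensity weights, and the planned balance check cannot reveal the distortion because it tests the distorted variable.

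In the simulated scenarios with pre-index relapse, weighting made the definitive group milder at diagnosis than its ATD comparator. With equal true severity this is a new imbalance of about 0.04 to 0.26 SD; with a true gap of 0.3 SD it is an over-correction to between −0.01 and −0.18 SD. These sizes rest on assumed relapse shares, relapse peaks, correlation and pretreatment share, and on a two-group model weighted on fT4 alone. The effect is zero for definitive patients without pretreatment.

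The documents do not support extending this to the primary outcome, since the weight trajectory is handled by joint modelling without these weights. Nor do they support a claim of demonstrated bias in any hazard ratio. The mechanism is certain but its size is not. Because the repair is nearly free, the definition should be changed before analysis.

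**What to change.** Change one line of Table 2: define baseline fT4 identically in all groups as the highest value from 3 months before diagnosis to the first antithyroid treatment of any kind (first ATD prescription or procedure, whichever comes first). Use that as the severity covariate in the propensity model.

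Handle later fT4 before the procedure in definitive patients under its own label, either as a separate variable or in a sensitivity analysis that repeats the weighting with the protocol's present definition. It would also help to report by group the length of the present window and the number of fT4 values in it, so that readers can judge how much the choice matters.

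Cost: no new data are needed. Relapse fT4 no longer enters through the baseline variable, and some patients may have no fT4 value in the shorter window, so the extent of missing values should be reported by group.

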**Figure 1 F1:**
[figure not shown]
Directed acyclic graph illustrating confounding in the study. The wide dark arrow indicates the relationship of interest. ATD, antithyroid drugs; IMD, Index of Multiple Deprivation; TFT, thyroid function test.

### Index date and follow-up

The index date in the cohort is the date of initiation of treatment for hyperthyroidism, which defines the treatment group (either ATD, radioiodine or thyroidectomy). There is a requirement of at least 12 months’ data available prior to the index date.

The natural history of weight changes will be modelled preindex and postindex date. While the follow-up for the analysis of outcomes will start at the index date, a minimum of 12-month follow-up is required for the inclusion.

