### Exposure

The exposure in the study is the treatment for hyperthyroidism. The study patients will be divided into three groups based on the treatment administered: (1) radioiodine: the allocation to this treatment arm will be assigned based on the Read code or OPCS-4 code of the treatment procedure for radioiodine; (2) thyroidectomy: the allocation to this treatment arm will be assigned based on the Read code or OPCS-4 code of the surgical procedure; (3) medical treatment arm will be identified based on the absence of radioiodine treatment code and thyroidectomy code in the presence of ATD treatment (based on the Read code or British National Formulary (BNF) code) longer than 6 months.

We anticipate good quality of ATD prescription and thyroidectomy. However, radioiodine, typically administered in outpatients, may be missed in a substantially high proportion of patients. Since ATD treatment does not incur permanent hypothyroidism, the long-term prescription of levothyroxine for hypothyroidism following treatment with ATD alone, that is, without any definitive procedures, will be considered as a proxy for radioiodine administration.

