#### Sensitivity to missed radioiodine record

Whenever ATD patients develop permanent hypothyroidism, a radioiodine treatment will be assumed, as explained in the Exposure section. All analyses will be repeated to check sensitivity to this assumption, excluding patients in the ATD group who developed hypothyroidism following medical treatment being the only antithyroid treatment on record.

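### Assigning radioiodine from later long-term levothyroxine leaves those patients without an index date and makes survival a condition of entry, biasing the mortality and event comparison in favour of radioiodine

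*Protocol article*

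**What the plan says.** Four statements in the Protocol article bear on this.

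- **Index date and follow-up.** The index date is "the date of initiation of treatment for hyperthyroidism, which defines the treatment group". For outcomes, "the follow-up for the analysis of outcomes will start at the index date", and "a minimum of 12-month follow-up is required for the inclusion".
- **Exposure, extent of missing records.** Radioiodine "may be missed in a substantially high proportion of patients". No figure is given.
- **Exposure, proxy rule.** The trigger is "the long-term prescription of levothyroxine for hypothyroidism following treatment with ATD alone" with no definitive procedure on record. Its consequence is that it "will be considered as a proxy for radioiodine administration".
- **Sensitivity to missed radioiodine record.** The proxy applies in the main analysis: "Whenever ATD patients develop permanent hypothyroidism, a radioiodine treatment will be assumed". All analyses are then to be repeated without these patients.

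Table 2 (Confounding) fixes age, smoking status, baseline fT4 and pretreatment ATD time relative to the index date. The section on cardiometabolic risks and mortality lists all four as candidates for the propensity model.

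**The concern.** The proxy rule creates radioiodine patients who, by definition, have no radioiodine record. The index-date rule needs the date of that treatment, and the article gives no substitute.

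The missing date is the visible symptom. The deeper problem is that exposure is decided by a later event. A patient with unrecorded radioiodine moves into the radioiodine arm only if he or she lives long enough to be prescribed long-term levothyroxine. A like patient who dies first stays in the ATD arm. If follow-up starts before the rule is met, the radioiodine arm is credited with time in which these patients could not have died. The ATD arm keeps the early deaths under any choice of index date. Both errors lower the radioiodine/ATD ratio.

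Cardiovascular and all-cause mortality and major cardiovascular events are named secondary outcomes, and comparing the three treatments is part of the study's overall aim. For non-fatal events, an index at ATD start would also count events that preceded radioiodine as radioiodine events.

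**Working it through.** The article gives no event counts, rates or treatment intervals, so there is no figure of the plan to reproduce. The check is a null model: no treatment effect, so an unbiased ratio is 1.00.

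**Inputs, all assumed:** death hazard h = 0.02 per year; observation to 10 years from ATD start; 30% of the cohort truly given radioiodine; 20-50% of that unrecorded; levothyroxine at 1 year plus an exponential time, overall mean 2 or 3 years. The 12-month rule is represented by starting every clock at 12 months.

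**Worked cell: 50% unrecorded, mean 3 years, landmark at 12 months.** Cohort shares are ATD 0.70, recorded radioiodine 0.15, unrecorded 0.15. After the landmark 9 years remain, and levothyroxine starts at rate m = 1/2 = 0.5 per year.

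- Any patient: deaths 1 - exp(-0.18) = 0.1647; person-years 0.1647/0.02 = 8.2365.
- Unrecorded patients dying before levothyroxine: h/(h+m) × [1 - exp(-0.52×9)] = 0.03846 × 0.9907 = 0.0381.
- Person-years of unrecorded patients who never meet the rule: 0.0701 (die first) + 9 × exp(-4.68) = 0.0835 (reach the end without levothyroxine), total 0.1536.
- Proxy patients: deaths 0.1647 - 0.0381 = 0.1266; person-years from the landmark 8.2365 - 0.1536 = 8.0829.
- Radioiodine arm: 0.15 × (0.1647 + 0.1266) / [0.15 × (8.2365 + 8.0829)] = 0.0437/2.4479 = 0.01785.
- ATD arm: (0.70 × 0.1647 + 0.15 × 0.0381) / (0.70 × 8.2365 + 0.15 × 0.1536) = 0.1210/5.7886 = 0.02091.
- **Ratio with ATD start as index: 0.01785/0.02091 = 0.85.**
- Proxy patients excluded: 0.0200/0.02091 = **0.96**.
- Delayed entry: unrecorded patients contribute (1 - exp(-4.68))/0.52 = 1.9052 person-years before levothyroxine. The ATD rate is then 0.1210/(0.70 × 8.2365 + 0.15 × 1.9052) = 0.1210/6.0513 = 0.0200, and the ratio is **1.00**.

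**Range.** Simulation of the same model agrees with these results:

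| Handling of proxy patients | 20% unrecorded, mean 2 y | 50% unrecorded, mean 3 y |
|---|---|---|
| Index at ATD start, no 12-month rule | 0.94 | 0.80 |
| Index at ATD start, 12-month landmark | 0.97 | 0.85 |
| Index at levothyroxine start, no landmark | 0.98 | 0.94 |
| Excluded, no landmark | 0.98 | 0.94 |
| Excluded, 12-month landmark | 0.99 | 0.96 |
| ATD until levothyroxine, then radioiodine | 1.00 | 1.00 |

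The levothyroxine-start row should be compared with the exclusion row without the landmark. They agree because, with a constant hazard and immediate classification, proxy patients followed from levothyroxine start die at the true rate. What remains is the early deaths left in the ATD arm.

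**Hypothyroidism at 80%.** The model gives levothyroxine to every unrecorded patient who lives long enough. The Introduction puts hypothyroidism after radioiodine at 80%. In the worked cell, 0.12 of the cohort can then be reclassified and 0.03 stays in ATD. Radioiodine: (0.15 × 0.1647 + 0.12 × 0.1266)/(0.15 × 8.2365 + 0.12 × 8.0829) = 0.0399/2.2054 = 0.01809. ATD: (0.73 × 0.1647 + 0.12 × 0.0381)/(0.73 × 8.2365 + 0.12 × 0.1536) = 0.1248/6.0311 = 0.02070. The ratio is 0.87 instead of 0.85.

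**Would a better date cure it?** A second null simulation used other assumptions: hazard 0.03, 40% given radioiodine, 40% of that unrecorded, radioiodine 0.5-2.5 years after ATD start, then on average 0.75 years to levothyroxine and a further 0.5 years to count as long-term. It compared proxy with recorded radioiodine patients. Without the 12-month rule, even the true radioiodine date gave 0.756/0.891 = 0.85, because entry still required survival to long-term levothyroxine. ATD start gave 0.634/0.891 = 0.71 (0.744/0.923 = 0.81 with the rule). Levothyroxine start gave 0.834/0.891 = 0.94 (0.906/0.923 = 0.98 with the rule).

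**The case against.** **The plan already tests this assumption.** It does. Repeating all analyses without the proxy patients leaves recorded radioiodine alone in that arm, and the section on natural history of weight changes also promises a check on missed treatment coding. In the model this brings the ratio to 0.99-0.96 with the landmark, so it would expose much of the bias. It is not a correction. Unrecorded radioiodine patients who died before levothyroxine remain in the ATD arm, the exclusion itself selects on hypothyroidism arising after baseline, and the main analysis is unchanged.

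**Any available date is about equally harmful.** A reader might infer this, but the documents do not support it. The index rule refers to the group-defining treatment, and the Population section treats ATD before radioiodine as pretreatment, so the plan's own logic points away from ATD start, the worst case. Levothyroxine start distorts mortality much less. It does drop early post-radioiodine events, and it dates the index-based covariates after the presumed procedure. The end of ATD is a third candidate, but it too requires survival to levothyroxine.

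**Only the radioiodine arm is affected.** This also goes too far. The early deaths left behind raise the ATD rate. Recorded radioiodine patients also had to survive to their procedure: in the second simulation they alone showed 0.89 against ATD, without the 12-month rule.

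**The article condenses an approved protocol that is not shown.** That protocol may hold a dating rule, and the lack of a date alone would be weak grounds. But the article itself fixes exposure by a later event, and no choice of date alone removes that.

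**Conclusion.** The point stands as a biased classification rule in the main cardiometabolic and mortality analyses, not merely as a missing detail. Under no true effect the radioiodine/ATD mortality ratio would be about 0.97-0.85 with ATD start as index and a 12-month landmark, and about 0.98-0.94 with levothyroxine start without the landmark. These sizes rest on the assumed 2% yearly mortality, 20-50% unrecorded radioiodine, 2-3 years to levothyroxine and a constant hazard. Allowing for 80% hypothyroidism shrinks them slightly. The direction, in favour of radioiodine, follows from the rule itself.

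The documents do not show that the published comparison must be seriously wrong: the index date that will be used is not stated, and a partial safeguard is planned. The change is advisable, with medium confidence in the size of the effect.

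**What to change.** In Exposure and in Index date and follow-up, define proxy radioiodine as a time-updated exposure for the cardiometabolic and mortality analyses. These patients count as ATD until the date on which the long-term levothyroxine rule is met, and enter the radioiodine risk set by delayed entry only from then. State when that rule is met.

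Handle pre-radioiodine ATD time, and the time at which propensity covariates are measured, by one common rule for recorded and proxy radioiodine patients. Setting proxy covariates at first treatment while recorded patients keep theirs at the radioiodine date would make pretreatment ATD time near zero for proxies only.

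Show the already planned analysis without proxy patients beside the main result.

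The cost is more coding, weights that must accommodate patients who contribute to both arms (the single baseline multinomial weight does not do this as described), and slightly wider intervals for radioiodine. No new data are needed.
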